## Abstract

**Background:**

Mental health symptoms among healthcare professionals (HCP) in intensive care units (ICUs) are a significant concern affecting both HCP well-being and patient care outcomes. Cross-sectional studies among members of the European Society of Intensive Care Medicine (ESICM) report up to 50% burnout rates. Determinants of burnout include communication, team cohesion, psychological support, and well-being promotion. We designed the 'Hello Bundle' intervention to mitigate burnout among ICU-HCPs by fostering positive social interactions and a supportive work environment. This justification synthesizes evidence from social psychology, positive psychology, and healthcare communication research to support the intervention. The 'Hello Bundle' aims to enhance interpersonal relationships, improve team cohesion, and reduce burnout rates. The six components include: Hello campaign posters, email reminders, integrating greetings in morning huddles, hello jars, lead-by-example initiatives, and a daily updated hello board in each ICU. This protocol describes a cluster randomized controlled trial to evaluate the effectiveness of the intervention.

**Methods:**

This protocol describes a cluster randomized controlled trial (RCT) conducted among ESICM-affiliated ICUs, consisting of at least 73 clusters with in average of 50 respondents per cluster, totaling approximately 7300 participants. Intervention clusters will implement the 6-component Hello Bundle between October 14 and November 10, 2024, while control clusters will be wait-listed to receive the intervention in January 2025 after the RCT concludes. Clusters will be matched based on ICU size (fewer or more than 20 beds), region, and average 2023 mortality. The primary outcome is the proportion of HCPs with burnout between intervention and control clusters at the end of the intervention. Secondary outcomes include comparing the following between clusters: (1) number of HCPs with high emotional exhaustion; (2) number with high depersonalization; (3) number with loss of accomplishment; (4) perception of ethical climate (5) satisfaction at work (VAS); (6) professional conflicts; (7) intention to leave the ICU (VAS); (8) patient-centered care rating; (9) family-centered care rating. The last secondary outcome is the comparison of burnout rates before and after the intervention in the intervention cluster. Outcomes will be based on HCP reports collected within four weeks before and after the intervention.

**Discussion:**

This is the first large trial of healthcare communication, social, and positive psychology intervention among ICU-HCPs. It holds the potential to provide valuable insights into effective strategies for addressing burnout in ICU settings, ultimately benefiting both HCPs and patients.

*Trial registration*: This trial was registered on ClinicalTrials.Gov on June 18, 2024. Registration: NCT06453616.

**Supplementary Information:**

The online version contains supplementary material available at 10.1186/s40635-024-00677-w.

## Introduction

### Background and rationale

Burnout among healthcare professionals (HCPs), particularly prevalent in the high-stress environment of the intensive care unit (ICU), is characterized by emotional exhaustion, depersonalization, and a decreased sense of personal accomplishment [1–4]. This phenomenon not only profoundly impacts the well-being of ICU staff but has substantial consequences on the quality of care [5]. Burnout can lead to decreased job satisfaction, increased turnover rates, and difficulties in recruitment, exacerbating existing staff shortages in critical care settings [6]. The consequences of burnout extend beyond individual HCPs, affecting team dynamics, communication, and, ultimately, patient and family outcomes [7]. In the ICU, where quick decision-making and effective teamwork are paramount, burnout among staff members can compromise the quality of care delivered to critically ill patients [5]. Additionally, burnout may contribute to medical errors, decreased patient satisfaction, and heightened morbidity and mortality rates. Thus, addressing burnout in the ICU is essential not only for safeguarding the HCP’s well-being but also for ensuring optimal patient care and mitigating the challenges posed by staff shortages.

In the ICU, burnout among HCPs is often associated with various mental health symptoms such as anxiety, depression, moral distress, and post-traumatic stress disorder (PTSD) [8, 9]. Therefore, a comprehensive approach that encompasses prevention, recognition (Table 1), reversal, and the cultivation of resilience is required to address mental health symptoms in ICU-HCPs [10]. Prevention efforts aim to create a supportive work environment and promote individual well-being from the outset, thereby mitigating the risk of burnout [11–13]. Strategies may include fostering open communication, providing access to resources for stress management and coping skills, and promoting work-life balance through flexible scheduling and support programs. However, despite preventive measures, burnout may still occur. Therefore, it is crucial to recognize the signs and symptoms of burnout early on through regular screening and assessments [14]. By identifying individuals at risk, interventions can be implemented promptly to prevent further escalation. Moreover, once burnout has developed, efforts to reverse its effects are essential. This may involve targeted interventions such as counseling, coaching, and peer support, as well as organizational changes to address systemic contributors to burnout. Additionally, building resilience among healthcare professionals is paramount in combating burnout and promoting long-term well-being [15, 16]. Resilience training programs can equip individuals with the skills and strategies needed to cope with stress, bounce back from adversity, and thrive in demanding healthcare environments. By adopting a proactive approach encompassing prevention, recognition, reversal, and resilience-building, healthcare organizations can effectively address burnout and support the well-being of ICU staff, ultimately enhancing patient care outcomes and mitigating the impact of staff shortages.

**Table 1 Tab1:** Common signs and symptoms associated with burnout among healthcare professionals

Signs of burnout	Description
Emotional exhaustion	Feeling emotionally drained, overwhelmed, and depleted of energy
Depersonalization	Developing negative, cynical attitudes and behaviors towards patients, colleagues, or work tasks
Reduced personal accomplishment	Experiencing a sense of ineffectiveness, low self-esteem, and diminished sense of achievement in one's work
Chronic fatigue	Persistent feelings of physical and mental fatigue, even after adequate rest
Increased irritability	Becoming easily frustrated, short-tempered, or impatient with colleagues, patients, or tasks
Difficulty concentrating	Struggling to focus, make decisions, or retain information, leading to decreased productivity and effectiveness
Withdrawal from work or social activities	Withdrawing from work-related tasks or social interactions, isolating oneself from colleagues and friends
Physical symptoms	Experiencing physical symptoms such as headaches, muscle tension, gastrointestinal issues, or changes in appetite or sleep patterns
Lack of motivation	Feeling apathetic, disengaged, and lacking enthusiasm or interest in work tasks or professional responsibilities
Increased Absenteeism	Taking more sick leave or absences from work than usual, often due to physical or mental health concerns related to burnout
Loss of empathy	Struggling to empathize with patients' or colleagues' experiences, emotions, or needs, leading to diminished quality of patient care

### ICU humanization and the aims of educational research

This project aims to encourage ICU personnel to adopt positive habits in their interactions with staff members. By disseminating the results in international scientific journals, we hope to enhance behavioral and communication skills among intensive care physicians and nurses, which are essential for the occupational well-being of healthcare workers.

The HELLO Trial seeks to drive cultural change in communication within ICU staff, creating a true partnership—a therapeutic alliance—to promote appropriate patient care, a positive work environment, and the psychological well-being of healthcare workers. As such, this protocol can be considered "educational research": it introduces best practices from a relational perspective among colleagues, while measuring their impact to gain scientific insights.

We believe that implementing the simple habits outlined in the HELLO Trial will help healthcare workers create a better ICU environment, potentially serving as a protective factor against burnout and helping staff members feel less isolated and stressed in their highly emotional daily work.

The new habits acquired during the HELLO Trial are intended to be sustained beyond the study's conclusion, maintaining the anticipated benefits. This study also provides intensivists the opportunity to create an international platform for idea exchange, with the potential to significantly improve the quality of planned interventions. If proven effective, this straightforward approach could serve as a model for ICUs worldwide.

### Design of the intervention

Few interventional studies have been conducted to prevent or mitigate burnout in HCPs. A systematic review and meta-analysis among physicians found that interventions were associated with only small reductions in burnout [17]. This study also suggested prioritizing organization-directed interventions that are delivered to experienced HCPs and in primary care. While mindfulness-based training was effective against burnout, it was ineffective in reducing anxiety or depression [18].

For this study, the dedicated steering committee from the European Society of Intensive Care Medicine (ESICM) aimed to design an intervention to reduce symptoms of burnout that would be feasible in ICUs globally and acceptable to ESICM members. Our steering committee considered four types of interventions: (1) organizational (staffing and workload management, work environment improvement through teamwork and communication, or training and development for resilience and professional growth); (2) individual (mindfulness and stress reduction through meditation and yoga, or health and wellness programs through physical fitness and healthy eating); (3) systemic (work-life balance policies, burnout awareness campaigns, mentorship programs, or peer support groups); and (4) technical (Electronic Health Records (EHR) optimization). As a teaching society aware of the devastating impact of burnout [19] and committed to prioritizing HCP well-being, maintaining a healthy workforce, and ensuring high-quality patient care [2], we selected an organizational intervention targeting the work environment (teamwork and communication). The "Hello Bundle" is a multi-faceted intervention designed to foster positive social interactions and a supportive work environment, through simple, cost-effective measures that are feasible in diverse global settings and structures.

### The "Hello Bundle": a 6-component intervention stemming from social psychology, positive psychology, and healthcare communication research

#### Theoretical framework

We aim to reshape HCP behaviors by reinforcing social norms and interactions within the ICU work environment. It is recognized that greetings and social niceties improve work atmosphere and climate, enhance emotional well-being and help build trust and cohesion among team members, which is essential for effective teamwork in high-stress environments like ICUs [20, 21]. The intervention also aims to influence how HCPs perceive their colleagues, give timely positive feedback, praise each other, and relate to each other. Additionally, we seek to change group dynamics in terms of conformity, leadership, and intergroup conflicts. The HELLO Bundle promotes positive emotions (happiness, joy, and contentment) and fosters individual strengths and virtues such as resilience, gratitude, and optimism. Positive emotions broaden individuals' thought-action repertoires, leading to greater resilience and reduced burnout [22]. We expect each component of the HELLO Bundle to enhance positive relationships, positively influence well-being and work satisfaction, and engage HCPs in activities that help achieve common professional goals [23]. Finally, effective communication is critical for successful teamwork in healthcare settings. Simple gestures like saying “Hello” can open channels for more meaningful communication, reducing misunderstandings and improving collaboration [24].

#### Intervention components and evidence

Hello campaign poster: will serve as visual cues (the posters), constant reminders of desired behaviors, reinforcing social norms and increasing the likelihood of engagement [25].

Email reminders: Twice weekly email reminders sent by the ESICM research staff act as behavioral prompts, encouraging consistent engagement with the intervention. This approach aligns with the principles of digital nudging [26].

Morning huddles: Incorporating greetings into morning huddles enhances team building and cohesion and sets a positive tone for the day. Morning huddles have been shown to improve communication and teamwork in healthcare settings [27].

Hello jar: The Hello Jar (Hello box) in which HCPs can leave messages for their colleagues provides a platform for positive reinforcement through recognition and appreciation, boosting morale and fostering a supportive work environment [28]. It can be seen as the Skinner box of modern times [29].

Lead by example: By using positive communication behavior, nursing and medical leaders can shape HCPs’ perceptions of the ICU and promote a stronger ICU climate. By greeting colleagues, they set a standard of model positive behavior for others to follow. Role modeling by leaders is crucial for shaping organizational culture [30].

Hello board: The Hello Board serves as an interactive tool for continuous engagement, promoting ongoing positive interactions and a sense of community among staff [11, 31].

#### Expected outcomes

Simple, low-cost interventions aimed at improving workplace interactions and social support can significantly reduce burnout among healthcare professionals [17], and improve job satisfaction by creating a positive work environment, leading to reduced turnover intentions [2, 32].

### Trial design

We designed a cluster RCT with a parallel design and 1:1 allocation ratio to evaluate the effectiveness of the HELLO bundle compared to a waitlist control group among at least 73 clusters of an average of 50 ICU-HCPs. Clusters will be matched based on ICU size (fewer or more than 20 beds) and country.

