### Methods: participants, interventions, and outcomes

#### Study setting and eligibility criteria of the participating ICUs

An invitation to participate in the HELLO RCT, along with two reminders, was sent to all ESICM affiliates. Responses indicating interest in the trial were received from 679 individuals working in 679 centers. The respondents were asked to:Identify a nurse–physician dyad who would act as local investigators for the trial.Complete a form detailing the characteristics of their ICU.Organize a unit-level meeting to provide information about the trial, including the type of intervention, the study timeline, and the nature of the data to be collected.Attend one of three videoconferences (or watch the recording) that provided information on the study design, the HELLO bundle, the burnout instrument, and associated questions.Obtain IRB approval and inform the local research department at each hospital.

Among the 679 centers that expressed interest in the trial, 434 completed the first four commitments and were subsequently randomized into either the intervention group (*n* = 217) or the control group (*n* = 217). Table 2 and Fig. 1 list the 434 ICUs that were randomized. As shown in Fig. 2, participation in the trial is contingent upon obtaining IRB approval, hence, we anticipated more centers than the 146 needed based on the sample calculation to avoid being underpowered.

**Table 2 Tab2:** Participating countries

Region	Number of sites	Region	Number of sites
*Africa* • Egypt 9 • Ethiopia 4 • Ghana 2 • Libya 2 • Morocco 9 • Nigeria 3 • South Africa 1 • Tanzania 1 • Tunisia 4 • Uganda 1	33	*Southern Europe* • Bosnia and Herzegovina 2 • Croatia 7 • Greece 20 • Italy 23 • North Macedonia 1 • Portugal 17 • Serbia 2 • Slovenia 3 • Spain 37 • Turkey 29	141
*Asia* • Bangladesh 5 • China 3 • India 44 • Malaysia 1 • Pakistan 5 • Philippines 1 • Singapore 2 • Taiwan 3 • Vietnam 1	65	*Middle East* • Bahrain 1 • Iran 1 • Iraq 2 • Israel 4 • Kuwait 3 • Saudi Arabia 13 • United Arab Emirates 7	31
*Northern Europe* • Denmark 1 • Estonia 1 • Ireland 6 • Lithuania 2 • United Kingdom 26	36	*North America* • Canada 2 • Dominican Republic 1 • Mexico 4 • Nicaragua 1 • Puerto Rico 1 • United States 10	19
*Western Europe* • Austria 6 • Belgium 2 • France 36 • Germany 6 • Switzerland 6	56	*Oceania* • Australia 2	2

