#### Sample size

Statistical analysis will compare outcomes between intervention and control groups, aiming to demonstrate a reduction in the prevalence of burnout from 39 to 30%, assuming an intra-class coefficient of 0.15, and aiming for a statistical power of 80% (Fig. 3). Intra-class coefficient for the outcome variable was approximated and liberal when compared to precedent cluster trials performed on burnout performed in other context [34].

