**Fig. 3 Fig3:**
[figure not shown]
Sample size estimation assuming 50 respondents per cluster, a reduction in the prevalence of burnout from 39 to 30%, assuming an intra-class coefficient of 0.15 (base intra-class coefficient, range 0.1–0.2)

Primary and secondary analyses will be performed at an individual level adjusting for clustering. No imputation will be performed for missing variables.

Subgroup analyses will be conducted to explore potential moderators of intervention effectiveness.

Assuming an intra-class correlation of 0.15, 146 centers and 50 respondents per center, the study would allow to demonstrate a reduction in burnout prevalence from 39 to 30% with a statistical power of 80%. This study will enroll at least *k* = 73 clusters of 50 participants in average, totaling approximately *n* = 7300 participants (assuming an average cluster size of *m* = 50). The sample size was determined by power calculations from previous cross sectional studies [3, 7, 35, 36]. Based on estimated effect sizes, ICCs, and SDs of the outcome in the population from previous data, and accounting for attrition related to failure to obtain IRB or local research committees approval, we estimated that at least *k* = 73 clusters and *n* = 7300 participants would be sufficient to detect significant effects with 80% power in the primary outcome. However, because there was an uncertainty about the proportion of IRB and local research committees’ failure, as well as the number of ICUs finally not willing to participate to the trial, we included all the 434 ICUs (217 per group) who applied to the IRB before July 1st, 2024.

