### Statistical methods

#### Primary and secondary outcomes

Data will be described as median and interquartile range (IQR) or number and percentage. Categorical variables will be compared using Fisher's exact test and continuous variables using the nonparametric Wilcoxon test, Mann–Whitney test, or Kruskal–Wallis test.

The primary method of analysis will be a generalized linear mixed-effects model, which will be adjusted for cluster. We will use an intention-to-treat approach with a binary exposure variable indicating if the participant was randomized to the intervention or control group.

Predefined subgroup analyses will include:Center and country effect as assessed using mixed effect model. Briefly, we will assessed effect of the intervention while accounting for center and country effect. Center and country will be examined in dedicated mixed effect model and will be added as random effect on the intercept. Impact of the intervention will be reported when adjusted for these confounders. Center and country effect will be reported [37]. To test for the significance of center and country effects on outcome, we will use permutation tests [38]. Difference in rate of burnout will across centers and countries will be reported as median odds-ratio with their confidence interval. Influence of centers and country will be plotted.In addition, influence of adherence to protocol will be assessed. Impact of adherence on outcome will be reported by quartile of adherence.Last, influence of the job of respondents will be assessed.

If any additional exploratory or sensitivity analyses should be performed, they will be reported in the manuscript as post hoc analyses and interpreted as exploratory hypothesis generating analyses.

We will use an appropriate bootstrapping method with an identity link. We will use two-tailed tests for all models with statistical significance thresholds of 0.05. Results will be reported as mean difference, incidence rate ratio or odds ratios as appropriate.

Statistical analyses will be performed with R statistical software, version 3.4.3 (available online at http://www.r-project.org/) and packages ‘lme4’,and’lmerTest’. A *p* value < 0.05 will be considered significant.

Results will be reported in adherence with standards for reporting implementation studies of complex interventions guidelines [39].

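### The minimum size is written as 73 clusters without "per arm"; the stated inputs need 73 per arm (146 in total), and that number contains no allowance for attrition

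*Protocol article*

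**What the plan says.** All references are to the Protocol article.

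- **Trial design:** the 1:1 parallel trial is conducted "among at least 73 clusters of an average of 50 ICU-HCPs". No arm is mentioned and no total is given.
- **Abstract, Methods:** the trial is described as "consisting of at least 73 clusters with in average of 50 respondents per cluster, totaling approximately 7300 participants".
- **Sample size (text after Fig. 3):** one sentence states the power claim as "Assuming an intra-class correlation of 0.15, 146 centers and 50 respondents per center". The next sentences return to a minimum of 73 clusters of 50, again paired with 7300 participants. They say that this number was reached "accounting for attrition related to failure to obtain IRB or local research committees approval".
- **Study setting and eligibility criteria:** 434 ICUs were randomised, 217 to each group, and taking part depends on ethics approval. The reason given for the surplus is that "we anticipated more centers than the 146 needed based on the sample calculation to avoid being underpowered".
- **Assignment of interventions: allocation:** 217 randomised clusters, which is the number in one group, are set against a target of 73.

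The words *per arm* or *per group* are not attached to 73 anywhere.

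**The concern.** Two numbers that differ by a factor of two are both given as the required number of clusters. The smaller one is the only one phrased as a minimum, and it is the only one in the Abstract and the Trial design section. The printed product is also wrong: 73 clusters of 50 do not make 7300.

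The final number of ICUs was open when the protocol was written, because participation depended on ethics approval and on willingness to continue, and the Sample size section calls both uncertain. Anyone who later compares the achieved number of ICUs with the plan needs one unambiguous figure. With the present text, a final count between 73 and 145 ICUs could be reported as reaching the cluster minimum while missing the number on which the 80% power rests.

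The attrition clause adds a second problem. It tells the reader that losses are already covered inside 73 and 7300. If they are not, those numbers must be met by ICUs that actually take part.

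**Working it through.** **Inputs**

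- Prevalence and ICC: "a reduction in the prevalence of burnout from 39 to 30%, assuming an intra-class coefficient of 0.15" (Sample size).
- Power: "aiming for a statistical power of 80"% (Sample size).
- Test: "We will use two-tailed tests for all models with statistical significance thresholds of 0.05" (Statistical methods). The Sample size section gives no alpha of its own, so I assume that this one applies.
- Cluster size m = 50, ICC range 0.10 to 0.20 (Fig. 3 legend); allocation 1:1 (Trial design).

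**Step 1. Reproduce the plan's figure**

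Individually randomised size per arm:

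- Unpooled variance: n = (1.960 + 0.842)² × (0.39 × 0.61 + 0.30 × 0.70) / 0.09² = 434.0
- Pooled variance under the null, no continuity correction: n = 437

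Design effect: 1 + (50 − 1) × 0.15 = 8.35.

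Clusters per arm = n × 8.35 / 50:

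- Unpooled: 434.0 × 8.35 = 3624 respondents; 3624 / 50 = 72.5
- Pooled: 437 × 8.35 = 3649 respondents; 3649 / 50 = 73.0

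Both round up to 73 **per arm**. That is 146 in total, and 146 × 50 = 7300. At 73 per arm the power is 80.0% (pooled) or 80.3% (unpooled). The 146, the 7300 and the 80% therefore belong together, and 73 fits them only as a per-arm number.

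**Step 2. Check the product as printed**

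73 × 50 = 3650, which is half of 7300.

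**Step 3. Power if 73 were the trial total**

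36.5 clusters per arm give 36.5 × 50 / 8.35 = 218.6 effective respondents per arm.

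SE = √[(0.39 × 0.61 + 0.30 × 0.70) / 218.6] = 0.0453

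Power = Φ(0.09 / 0.0453 − 1.96) ≈ 0.51

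| ICC | 73 per arm (146 in total) | 73 in total |
|---|---|---|
| 0.10 | 91.6% | 65.4% |
| 0.15 | 80.0% | 50.8% |
| 0.20 | 69.3% | 41.3% |

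(Pooled variance. At ICC 0.15 and 73 in total, the unpooled form gives 51.1% and a t-based form 50.0%.)

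**Step 4. Look for a reading that makes 73 in total correct**

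- One-sided test: 57.4, so 58 clusters per arm. This still does not give 73 in total, and the protocol specifies two-sided tests.
- 73 clusters sharing 7300 people, so 100 per cluster: the design effect is 1 + 99 × 0.15 = 15.85 and power is about 53%. It also contradicts the stated average of 50.

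Neither restores 80% power.

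**Step 5. Look for an attrition allowance**

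73 per arm supplies 73 × 50 = 3650 respondents. The formula needs 3624 (unpooled) or 3649 (pooled). The surplus is 26 or 1 respondents per arm, less than one cluster of 50, and comes only from rounding up. Nothing in 73 per arm or 7300 covers ICUs lost to failed approval.

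**The case against.** The strongest reply is that this is a dropped qualifier in a correctly sized trial. Most of that stands:

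- The correct total of 146 is printed twice, in the Study setting and Sample size sections.
- The 7300 printed beside 73 equals 146 × 50, so the Abstract and Sample size section carry a figure that points to the right total. Only the Trial design section gives 73 with nothing to reconcile it.
- The allocation text compares 73 with 217, the per-group number, which makes sense only if 73 is also per group.

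A reader might infer that the trial is planned with about 51% power. The documents do not support that. Ending with 73 ICUs would mean losing 361 of the 434 randomised (361 / 434 = 83%). Even falling below 146 requires losing more than 288 (288 / 434 = 66%).

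A reader might also infer that 73 works as a threshold for closing recruitment or going ahead. No section ties any such decision to it: all 434 ICUs were already randomised and the intervention dates are fixed. Nor would 73 ICUs of 50 satisfy the whole written minimum, since the Sample size section joins 73 clusters to 7300 participants.

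On attrition, the same section and the Study setting section already present the 434 ICUs as the protection against loss. That makes the clause easy to remove, but it does not make it true.

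The reply does not remove the error. The printed arithmetic is false in two sections, and the reader has to work out which of two cluster numbers is meant.

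**Conclusion.** The point holds as an error in the stated minimum, not in the power calculation. The inputs reproduce 73 clusters per arm, 146 in total and 7300 respondents for 80% power. Written without *per arm*, the minimum is half of what is needed, and its product with 50 is 3650, not 7300. Taken literally it would give about 51% power at ICC 0.15 (65% at 0.10, 41% at 0.20). That figure shows the size of the ambiguity; it does not forecast the trial's power.

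The statement that 73 and 7300 account for attrition is wrong under either reading of 73.

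The result assumes two-sided 0.05, equal clusters of 50 and no continuity correction; with the correction the requirement would be 77 per arm. That 73 is meant per arm is an inference, though a strong one, because no section says so. This should be fixed; the randomisation, the analysis and the intended target are unaffected.

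**What to change.** 1. In the Abstract (Methods), Trial design and Sample size sections, replace the 73-cluster wording with: *at least 73 clusters per arm (146 in total), about 7300 respondents*.
2. In the Sample size section, delete the clause saying that these numbers allow for failed ethics or local approval. The existing text on the 434 randomised ICUs then stands as the allowance.
3. In the allocation section, say that 217 clusters per arm (434 in total) were randomised against a target of 73 per arm (146 in total).

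There is no need to print the 51% figure in the protocol. The cost is wording only, with no extra recruitment, no new calculation and no change to the analysis.
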